### Randomisation

A randomisation list is computer generated by an external statistician. The patients are randomised in blocks of ten, to secure equal distribution in the two groups in each department. Assignments are enclosed in sequentially numbered, opaque, sealed envelopes. When a patient is included an envelope is opened sequentially and the patient's initials and identification number written on the assignment. The patients are enrolled and treatment assignment ascertained by the primary investigator or any of his/her delegated at each centre. The envelopes are generated by the coordinator and afterwards the allocation list is packed in a sealed, opaque envelope and stored by the coordinator.

### Blinding

This is an open-label study.

### Statistical methods

The frequency of reaching a 30% reduction in iPTH for a minimum of 4 weeks is compared between the two treatments in the same person by McNemar test for paired observations. It is tested whether the effect is dependent of the order of the periods.

Furthermore the effect of the two treatments after the first period will be analysed separately from the second period.

The distribution of the variables and the changes in the variables from the start until the end will be described. Mean, median, standard deviation and range will be reported.

All tests are two-sided tests α = 0.05. The changes during the two treatments will be compared using tests for paired observations.

Parametric tests (paired t-test) will be used if the distributions are normal and non-parametric test (McNemar test and Wilcoxon signed ranks test) for ordered or continuous data.

All participants that are evaluable will be included in the statistical analysis.

The analysis will be performed in Statistica with the procedures: UNIVARIATA, FREQ and ANOVA.

The data analysis will be performed blinded. While doing the statistical analysis the treatment groups will be unknown.

All data will be described and the reason for missing values will be described. Every violation from the statistical plan will be described in the final publication.

All eligible subjects receives a written description of the study objective, schedule, benefits and risks, other treatment possibilities, funding and contact information.

They are offered a consultation providing further information. Here they can bring their relatives.

If the subject agrees to participate a written informed consent is signed.

The study is in compliance with the Helsinki Declaration and is approved by the Danish National Committee on Biomedical Research Ethics (SJ-27), the Danish Medicines Agency (EudraCT: 2006-005981-37) and Danish Data Protection Agency (2007-41-0503)

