### Interventions

The study design is a crossover design where the patients are randomised into two treatment arms (Figure 1). The randomisation is performed after 6 weeks wash out during which the patients are not allowed to receive any kind of vitamin D supplement. The first arm receives alfacalcidol for 16 weeks and then goes through another 6 weeks wash out period before they receive paricalcitol for 16 weeks. The second arm receive paricalcitol for 16 weeks and then goes through another 6 weeks wash out period before they receive alfacalcidol for 16 weeks. The drugs are given at the end of haemodialysis treatment two or three times a week depending on the frequency of haemodialysis treatment. The start dose of alfacalcidol (Etalpha^®^Injection) is 3 μg a week and the start dose of paricalcitol (Zemplar^®^Injection) is 9 μg a week. Every second week the dose is titrated 50% according to p-phosphate, p-calcium and p-iPTH. As long as p-phosphate <1.8 mmol/l and ionised p-calcium <1.30 mmol/l and p-iPTH>150 pg/ml the dose is increased. When p- iPTH ≤ 150 pg/ml and p-phosphate <1.8 mmol/l and ionised p-calcium <1.35 mmol/l the dose is retained. If at any time p-phosphate >1.8 mmol/l or ionised p-calcium >1.35 mmol/l in two repeated measurements the dose is reduced.

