### Outcomes

The primary efficacy end point is the proportion of patients achieving ≥ 30% reduction in iPTH from baseline until the last 4 weeks of treatment with alfacalcidol or paricalcitol. The secondary outcomes is changes in ionised p-calcium, p-phosphate, calcium × phosphate product, p-alkaline phosphatase, p-25(OH)vitamin D, p-1,25(OH)_2_vitamin D, blood pressure, pulse and pulse pressure from baseline until the end of treatment with alfacalcidol or paricalcitol respectively. The frequency of parathyroidectomy or need for calcimimetics is registered.

Safety endpoints are b-haemoglobin, b-leukocytes, b-trombocytes, p-sodium, p-potassium, p-magnesium, p-bicarbonate, p-creatinine, p-urea, urea reduction rate, p-albumin, p-alanine aminotransferase, p-bilirubin, p-C-reactive protein and weight measured at the beginning and after each treatment period.

All laboratory samples are drawn from the blood lines of the dialyzer before start of the dialysis. P-iPTH, ionised p-calcium and p-phosphate are measured every second week during the treatment periods, the others parameters are measured at the beginning and the end of each treatment period. The urea reduction rate is calculated from a urea measured before dialysis and a urea measured immediately after dialysis. All laboratory analyses are performed at the participating departments' local laboratories.

Blood pressure and pulse are measured after 5 minutes rest before dialysis, and weight is measured before the dialysis session with clothes but no shoes.

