### Sample size

We assume that the proportion of patients achieving ≥ 30% reduction in iPTH in the last four weeks of the treatment period would be 50% in the alfacalcidol group and 68% in the paricalcitol group [13,14]. Based on 0.8 power to detect a significant difference (P = 0.05, McNemars test), 117 patients is required for inclusion.

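### The primary McNemar test is written for a 4-week duration of response with no time window, while the declared and powered endpoint is response in the last 4 weeks of treatment

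*Protocol article*

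**What the plan says.** The protocol article describes the primary responder in three places.

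- **Outcomes** names the primary efficacy endpoint as the "proportion of patients achieving ≥ 30% reduction in iPTH from baseline until the last 4 weeks of treatment with alfacalcidol or paricalcitol".
- **Sample size** uses the same window. It concerns patients "achieving ≥ 30% reduction in iPTH in the last four weeks of the treatment period", a proportion that "would be 50% in the alfacalcidol group and 68% in the paricalcitol group", and derives 117 patients for a McNemar test with power 0.8 at P = 0.05.
- **Statistical methods** opens with the primary analysis: "The frequency of reaching a 30% reduction in iPTH for a minimum of 4 weeks is compared between the two treatments", within the same person, by the McNemar test.

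Two further statements bear on whether these descriptions can diverge. On sampling, Outcomes says: "P-iPTH, ionised p-calcium and p-phosphate are measured every second week during the treatment periods". On dosing, Interventions says: "If at any time p-phosphate >1.8 mmol/l or ionised p-calcium >1.35 mmol/l in two repeated measurements the dose is reduced".

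**The concern.** Outcomes and Sample size fix a time window. Statistical methods fixes a duration and gives no window, and nothing in the article says which takes precedence. A patient can satisfy one description and fail the other.

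The patients affected matter to this trial. Its hypothesis is about suppressing iPTH without raising calcium or phosphate, and a dose cut for calcium or phosphate is one way in which an early response could be lost before the end of the period. If the confirmatory test counts a different event from the one declared and powered, the result does not answer the stated question, and its power is unknown because no rates are given for the duration rule.

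**Working it through.** **1. The plan's own sample size.** Inputs from Sample size and Statistical methods: p1 = 0.50, p2 = 0.68, difference d = 0.18, two-sided alpha 0.05 (z = 1.960), power 0.80 (z = 0.8416). The article gives no within-patient correlation, so independence is assumed here.

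- Discordant share: ψ = 0.50 × 0.32 + 0.50 × 0.68 = 0.16 + 0.34 = 0.50.
- Miettinen formula: n = [1.960ψ + 0.8416√(ψ² − d²(3 + ψ)/4)]² / (ψd²) = [0.980 + 0.8416 × √0.22165]² / 0.0162 = 1.894 / 0.0162 = 116.9, so 117.
- Connor formula: n = [1.960√ψ + 0.8416√(ψ − d²)]² / d² = 118.7, so 119. Power at 117 is 0.794.

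The figure of 117 reproduces, for rates stated for the last-4-weeks responder. About 117 × 0.50 = 58.5 discordant pairs are then expected, split about 39.8 (117 × 0.34) to 18.7 (117 × 0.16).

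**2. Can the two descriptions disagree on one patient?** Sixteen weeks of two-weekly readings give 16/2 = 8 values. The last 4 weeks are taken as weeks 12, 14 and 16. A 4-week duration is taken as three consecutive readings at or below 0.70 of baseline. The invented values below are fractions of baseline.

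| Patient | Readings | Last-4-weeks mean | Three consecutive readings ≤ 0.70 |
|---|---|---|---|
| A | weeks 6, 8, 10: 0.65 each; weeks 12, 14, 16: 0.80, 0.85, 0.85; earlier weeks above 0.70 | 2.50/3 = 0.83, non-responder | yes, responder |
| B | weeks 12, 14, 16: 0.80, 0.72, 0.55; earlier weeks above 0.70 | 2.07/3 = 0.69, responder | no, non-responder |

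Disagreement is possible in both directions. Patient B depends on reading the window as a mean, which the article does not state.

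**3. How often, on assumed inputs?** This is an illustrative simulation of 300,000 patient-periods per scenario. All inputs are assumed: log-normal iPTH; between-patient SD 0.45 and within-patient SD 0.2 or 0.3 on the log scale; typical final log change −0.357 (a 30% reduction) or −0.60 (45%); and a course that either rises to a plateau at week 12 or peaks at week 10 and then partly fades.

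| Course | SD | Log change | Last-4-weeks mean | Any 4-week run | Classified differently |
|---|---|---|---|---|---|
| plateau | 0.2 | −0.357 | 49.0% | 42.3% | 9.3% |
| plateau | 0.2 | −0.60 | 67.5% | 60.5% | 9.0% |
| plateau | 0.3 | −0.357 | 48.0% | 41.9% | 11.5% |
| plateau | 0.3 | −0.60 | 64.5% | 57.3% | 11.4% |
| fading | 0.2 | −0.357 | 51.8% | 51.4% | 9.1% |
| fading | 0.2 | −0.60 | 71.7% | 75.0% | 8.6% |
| fading | 0.3 | −0.357 | 50.4% | 50.1% | 11.7% |
| fading | 0.3 | −0.60 | 68.5% | 70.5% | 10.9% |

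Between 8.6% and 11.7% of patient-periods change class. With 2 × 117 = 234 periods that is about 20 to 27. The net responder rate under the any-run rule ranges from 7.2 points lower (64.5% to 57.3%) to 3.3 points higher (71.7% to 75.0%).

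**4. What this implies for the treatment difference.** Subtract the rates for log change −0.357 from those for −0.60.

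- Same course for both drugs: the any-run rule changes the difference by between −1.1 points (plateau, SD 0.3: 15.4 against 16.5) and +3.7 points (fading, SD 0.2: 23.6 against 19.9).
- Different courses: the change runs from about −7 points (SD 0.3, fading for the weaker and plateau for the stronger effect: 7.2 against 14.1) to +10 points (SD 0.2, the reverse: 32.7 against 22.7).

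The sign depends on assumed courses about which the article says nothing. These are differences of simulated rates; no McNemar comparison was simulated.

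**The case against.** The strongest reply is that Statistical methods never says the 4 weeks may fall anywhere. It may be shorthand for a reduction sustained through the last 4 weeks. All three places share the 30% and the 4 weeks, and two of them agree on the window, including the one that names the endpoint. The Discussion also says the period was chosen to be long enough for steady-state suppression, which fits an end-of-period assessment. This stands in part: a response at any time is a reading of an open phrase, and the sentence is better called incomplete than irreconcilable. But it states no window, and it is the only sentence that specifies the confirmatory test. Even the charitable reading leaves open whether every reading or an average must qualify.

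Three stronger inferences should be resisted.

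- **The duration rule favours the more calcaemic drug.** This is not shown. In a separate illustrative simulation in which 30% of patients lost 60% of their effect after week 10, responder rates were about 45% for the last-4-weeks mean and 44–45% for any 4-week run. Which drug is more calcaemic is also part of what the trial asks.
- **The responder rate moves by up to 13 points.** That figure needs a rule that weeks 12, 14 and 16 must all qualify, which the article nowhere states. A shift in one rate is also not a shift in the difference between treatments, and a shift common to both drugs largely cancels.
- **The open-label design leaves the definition free to be chosen after the results are seen.** The article plans analysis with the treatment groups unknown and promises to report departures from the plan. These safeguards reduce the scope for selective choice. They do not remove it, since masked labels do not hide which definition gives the smaller P value.

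**Conclusion.** The point holds as a mismatch between the declared, powered endpoint and the sentence that specifies its test. Read literally, that sentence can count patients who are non-responders under the endpoint definition. On assumed inputs and a mean-based reading of the window, about 9% to 12% of patient-periods change class.

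A reader might infer that the same data must give a different trial result. The article does not support that: the two rules can lead to different conclusions but need not, and neither the size nor the direction of an effect on the comparison can be derived from it. A reader might also infer that the sample size is wrong. It is not: 117 reproduces under independence and is tied to the last-4-weeks responder. If the duration rule were really intended, the number could not be recomputed, because no rates are given for it.

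**What to change.** Before analysis, amend the first sentence of Statistical methods so that the McNemar test compares the proportion of patients with at least a 30% iPTH reduction in the last 4 weeks of each treatment period, as in Outcomes and Sample size.

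In the same place the sponsor should state two things that the article leaves open: which measurement is the baseline, and how the two-weekly readings in the window are combined. Their mean is one example. It is the sponsor's choice and not something that the sample-size text already fixes.

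Keep the 4-week duration rule, with its own window spelled out, only as a named sensitivity analysis.

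The cost is a sentence or two in the protocol, carried into any analysis plan. It needs no new data, and the sample size stays at 117.

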## Methods/design

### Participants

Eligible subjects are > 18 years old and receiving chronic haemodialysis therapy for at least 3 month prior to screening in any of nine Danish haemodialysis outpatient clinics. After a period of minimum 6 weeks wash out, without any kind of vitamin D supplement, and sufficiently regulated p-phosphate (<1.8 mmol/l) and ionised p-calcium (<1.25 mmol/l), the patients are candidates for inclusion if p-iPTH is >350 pg/ml (37,1 pmol/l). The maximal allowed dose of calcium-containing phosphate-binders is 1600 mg elementary calcium a day at the time of inclusion. The patients may not be scheduled for parathyroidectomy or planned to start treatment with calcimimetics according to the local guidelines in the participating departments. Anticonception and negative pregnancy test should be present for fertile women. They are not admitted to the study if any of the following criteria are present (1) malignancy during the past five years (2) expected survival less than one year (3) pregnancy or breast feeding (4) allergy to any ingredient of Etalpha^® ^or Zemplar^® ^(5) in treatment with calcimimetics (6) participating in any other clinical trials which could affect the endpoints.

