**Figure 1 F1:**
[figure not shown]
**Flow chart for comparative cross-over study of alfacalcidol and paricalcitol**. After a 6 week wash out period, 117 patients are included. Every participating patient receives 16 weeks of treatment with alfacalcidol and 16 weeks of treatment with paricalcitol. The order of the treatments is decided by randomisation.

After inclusion the dose of calcium-containing phosphate-binders can only be unchanged or reduced. Elevated p-phosphate should be treated thoroughly with calcium-free phosphate-binders, dietary intervention and re-evaluation of the dialysis dose. Elevated p-calcium should lead to dietary intervention and reduction of calcium containing phosphate binders. The calcium concentration of dialysate is fixed to 1.25 mmol/l.

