## Discussion

This article describes the protocol of a randomised trial comparing the ability of alfacalcidol and paricalcitol to suppress secondary hyperparathyroidism without causing hypercalcemia and hyperphosphatemia in patients with chronic kidney disease. As far as we know, alfacalcidol and paricalcitol have never been compared in a randomised clinical trial before.

The advantage of the cross-over design is an elimination of the stochastic variation due to differences between individuals. This reduces the sample size needed. In Denmark in year 2007, there was 2037 haemodialysis patients and a death rate of 21.7% per year in this patient group [15]. Therefore, limiting the sample size is necessary.

When deciding the length of the treatment period it was a balance between different considerations. First, it should not be too long to avoid too many patients to drop out before completing the study. With a mortality rate of 21.7% a year, this is a problem [15]. Second, the treatment period should be long enough to reach a steady state in parathyroid hormone suppression. Going through other long term interventional studies with alfacalcidol or paricalcitol, 16 weeks seems to be the minimal feasible length [6,16]. Third, there is a risk of progression of the secondary hyperparathyroidism over time. However, secondary hyperparathyroidism is a chronic disease. The disease should not progress in a period of 44 weeks, as long as the patients are treated with some kind of active vitamin D.

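### The primary McNemar test and the paired tests carry no period term, so any period effect shifts the estimate when sequence groups are unequal and makes the tests conservative when they are equal

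*Protocol article*

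**What the plan says.** The Statistical methods section of the protocol article fixes the primary analysis: the frequency of a 30% iPTH reduction is compared within patient "by McNemar test for paired observations. It is tested whether the effect is dependent of the order of the periods". For the other outcomes, "The changes during the two treatments will be compared using tests for paired observations", by paired t-test or Wilcoxon signed ranks test. The analysis set is the evaluable participants.

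Two further steps concern order and period:
- The order test just quoted. The article states no consequence of its result.
- "Furthermore the effect of the two treatments after the first period will be analysed separately from the second period". The Discussion gives a possibly inadequate wash-out as the reason.

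Other sections bear on whether the periods are alike:
- Under Participants, patients are "candidates for inclusion if p-iPTH is >350 pg/ml (37,1 pmol/l"), with upper limits on phosphate and ionised calcium. These limits are stated for inclusion only.
- The text below Figure 1 adds: "After inclusion the dose of calcium-containing phosphate-binders can only be unchanged or reduced".
- The Discussion raises progression over time and sets it aside: "The disease should not progress in a period of 44 weeks, as long as the patients are treated" with active vitamin D.

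**The concern.** In a two-period crossover, the within-patient difference between drugs also contains the difference between periods, with opposite sign in the two sequences. A pooled paired test relies on these contributions cancelling. They cancel in the estimate only if the evaluable sequence groups are equal. Even then, they stay in the variance that the test uses.

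There are reasons to expect the periods to differ:
- An iPTH threshold applied only at entry lets regression to the mean act mainly on the period 1 baseline.
- Phosphate and calcium drive titration, and both are required to be controlled at the start of period 1; no such requirement is stated for period 2.
- The binder rule allows change in one direction only.
- The argument for stable disease is conditional on treatment, yet one 6-week untreated interval lies between the periods.

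At stake are a small shift in the main estimate, in either direction, and some avoidable loss of power.

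**Working it through.** **1. The plan's own figure.** Sample size section: 50% v 68%, two-sided alpha 0.05, power 0.80, McNemar. With responses independent within patient, the discordant share is ψ = 0.50×0.32 + 0.68×0.50 = 0.50 and the difference is Δ = 0.18. Miettinen's formula, n = [1.96ψ + 0.842√(ψ² − Δ²(3+ψ)/4)]² / (ψΔ²), gives (0.980 + 0.396)² / 0.0162 = 116.9, so 117. The stated number reproduces, and it assumes no period effect.

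**2. Shift in the estimate.** Let δ be the period 1 minus period 2 response rate, n1 the evaluable patients with alfacalcidol first and n2 those with paricalcitol first. The expected paricalcitol minus alfacalcidol difference is Δ − δ in the first sequence and Δ + δ in the second.
- Pooled: Δ − δ(n1−n2)/(n1+n2).
- Average of the two sequence-specific differences: Δ, whatever the split.

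The documents give no δ, so 10 and 20 points are assumptions. Absolute shift in points:

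| Split | δ = 10 | δ = 20 |
|---|---|---|
| 59:58 | 10×1/117 = 0.1 | 0.2 |
| 64:53 | 10×11/117 = 0.9 | 1.9 |
| 45:55 | 10×10/100 = 1.0 | 2.0 |
| 40:60 | 10×20/100 = 2.0 | 4.0 |

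**3. Size with equal groups.** McNemar takes the variance per pair as the discordant share ψ; the true value under no treatment effect is ψ − δ². With a mean response of 59% (midway between 50% and 68%) and independent responses:
- δ = 0.10: rates 0.64 and 0.54, ψ = 0.64×0.46 + 0.54×0.36 = 0.489. √(0.479/0.489) = 0.990, effective cut-off 1.96/0.990 = 1.98, size 0.048.
- δ = 0.20: rates 0.69 and 0.49, ψ = 0.69×0.51 + 0.49×0.31 = 0.504. √(0.464/0.504) = 0.959, cut-off 2.04, size 0.041.

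**4. Simulation** (200,000 replicates per setting; size over within-patient correlation 0 and 0.3; power at 50% v 68%, correlation 0; period 1 response the higher):

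| Split (n1:n2) | δ | McNemar size | Prescott size | McNemar power | Prescott power |
|---|---|---|---|---|---|
| 59:58 | 0 | 0.049–0.050 | 0.050 | 0.800 | 0.801 |
| 59:58 | 10 | 0.046–0.047 | 0.050 | 0.793 | 0.803 |
| 59:58 | 20 | 0.038–0.041 | 0.050 | 0.784 | 0.818 |
| 64:53 | 0 | 0.049 | 0.049 | 0.801 | 0.798 |
| 64:53 | 20 | 0.049 | 0.050 | 0.695 | 0.813 |
| 40:60 | 0 | 0.050–0.051 | 0.049 | 0.735 | 0.718 |
| 40:60 | 20 | 0.075–0.087 | 0.049 | 0.884 | 0.739 |

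At 64:53 and δ = 20, a true 18.0 points is estimated as 16.1. With the split reversed it becomes 19.9, and McNemar's power is 0.87. McNemar's power moves with the direction of the shift, so its higher value at 40:60 reflects bias and is not a gain. The average of the sequence-specific differences was unbiased throughout. Mainland-Gart also kept its size (0.050–0.053 for δ up to 20) but at 59:58 gained little power over McNemar (0.789 v 0.784 at δ = 20).

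The paired t-test behaves likewise: at 59:58 its size is 0.044 and 0.027 for period effects of 0.25 and 0.5 SD of the within-patient difference.

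**5. How unequal the groups may be.** Nine centres and 117 patients give 13 per centre on average, so blocks of ten are left incomplete. Before any loss, n1−n2 has SD about 4.6; its absolute value has median 3, 95th percentile 9 and 99th percentile 11. Mortality of 21.7% a year over 16 + 6 + 16 = 38 weeks leaves 117 × 0.783^(38/52) ≈ 98. With loss unrelated to sequence, 45:55 or worse arose in 7–12% of simulated trials and 40:60 or worse in 0.04–0.24%.

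**6. How large the period effect may be.** Regression to the mean from the entry threshold raised period 1 response by 2 to 13 points, under assumed log-SDs of 0.15–0.35 within and 0.5–0.7 between patients, with the qualifying reading as baseline and two end readings averaged. Requiring two or three consecutive readings to meet the reduction, with no drug effect, gave a gap of about 1 to 7 points.

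**The case against.** The strongest reply is that the plan attends to order. It tests for it, and its first-period comparison between randomised groups is free of any period effect. A reader might infer that the period is ignored altogether; the article does not support that. What stands is narrower: neither step changes the primary estimate. The first-period analysis cannot take its place either. With 59 and 58 patients, 0.18 / √(0.50×0.50/59 + 0.68×0.32/58) = 2.01, a power of about 0.52.

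A reader might also infer that the type I error is inflated. It is not, short of an extreme split. With equal groups the error is conservative, and at 64:53 the size stays near 0.05 although the estimate is shifted. If loss is unrelated to sequence, the shift is random in sign and averages zero over repeated trials. At the median imbalance of 3 it is only 20 × 3/117 = 0.5 points for a 20-point period effect.

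Finally, it is an inference from the entry limits and the binder rule that the design produces a period effect. The article states no size, nor that the qualifying reading serves as the period 1 baseline. Each period follows a wash-out of the same length, so the 12 untreated weeks in 44 do not by themselves separate the periods. The requirement that the reduction last at least 4 weeks weakens regression to the mean. All of this limits the size of the point; none of it puts a period term into the named tests.

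**Conclusion.** The point holds as a modest but real weakness in a method that the article fixes. If a period effect of 10 to 20 points exists, the primary estimate moves by about 1 to 2 points at 64:53 or 45:55. With equal groups, McNemar runs at about 0.038 to 0.047 and has about 1 to 3 points less power than Prescott's test. With a small period effect and near-equal groups the impact is negligible. These sizes rest on an assumed period effect, a mean response of 59% and within-patient correlation of 0 to 0.3. The documents do not show that a period effect exists, that loss depends on sequence or that the trial's conclusion would be invalid. The case for change is that the correction is nearly free.

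**What to change.** - Make the primary comparison a period-adjusted test by randomised sequence. Prescott's test compares the within-patient period difference (−1, 0, +1) between sequences and uses all patients with both periods. Mainland-Gart is an alternative, with less power in the settings above.
- Report the treatment difference as the average of the two sequence-specific differences, with a 95% CI.
- For continuous changes, use the Hills-Armitage comparison by sequence, or a crossover model with a period term.
- Keep McNemar as a sensitivity analysis and the first-period comparison as supportive.

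The cost is a change of wording. The sequence is already randomised and recorded, so no new data or visits are needed. The only statistical cost arises when there is no period effect and the groups are unequal: power 0.798 v 0.801 at 64:53, and 0.718 v 0.735 at the remote 40:60.

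### Continuous outcomes are compared by unadjusted paired tests on change from baseline, and no continuous iPTH comparison is specified as an outcome: valid, but it gives away precision that scheduled data would provide

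*Protocol article*

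**What the plan says.** The Outcomes section makes the primary end point a responder rate: "the proportion of patients achieving ≥ 30% reduction in iPTH from baseline until the last 4 weeks of treatment". The Statistical methods section says that this response "is compared between the two treatments in the same person by McNemar test for paired observations".

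The continuous outcomes are defined as changes from baseline. The list begins "The secondary outcomes is changes in ionised p-calcium, p-phosphate, calcium" and continues with the calcium × phosphate product, alkaline phosphatase, two vitamin D measurements, blood pressure, pulse and pulse pressure. iPTH is not in it.

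The comparison of these outcomes is then fixed: "The changes during the two treatments will be compared using tests for paired observations". The paired t-test applies if distributions are normal. The alternative is a "non-parametric test (McNemar test and Wilcoxon signed ranks test) for ordered or continuous data". No baseline covariate or period term is given for these comparisons. ANOVA appears only as the name of a software procedure, without a model. The level is set by "All tests are two-sided tests α = 0.05".

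The Outcomes section also schedules iPTH, ionised calcium and phosphate every second week during treatment, and the other parameters at the start and end of each period.

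**The concern.** In a crossover each patient is already his or her own control. Subtracting the period's own baseline brings two more variable readings into the treatment contrast. Whether that helps or hurts depends on how strongly baseline and end value move together within a period. Using the baselines as a covariate lets the data set that weight, where subtraction fixes it at one.

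This matters here because the hypothesis under Objectives is suppression of hyperparathyroidism without raised phosphate and calcium. The calcium and phosphate contrasts therefore carry half the question. The Discussion justifies the crossover by the removal of between-patient variation and the need to limit sample size, so an analysis that returns part of that gain works against the design.

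For iPTH, the variable treatment is meant to act on, the only specified comparison reduces each period to yes or no. If the responder comparison is inconclusive, a continuous iPTH comparison that was not pre-specified would look post hoc.

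Separately, McNemar is a test for paired binary data, so naming it for ordered or continuous data is a slip.

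**Working it through.** **1. The plan's own figure.** The Sample size section assumes that response "would be 50% in the alfacalcidol group and 68% in the paricalcitol group" and concludes: "Based on 0.8 power to detect a significant difference (P = 0.05, McNemars test), 117 patients is required for inclusion". With independent responses within a patient, the discordant cells are 0.50 × 0.32 = 0.16 and 0.68 × 0.50 = 0.34, so discordance ψ = 0.50 and difference d = 0.18.

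- Miettinen formula: n = [1.960ψ + 0.842√(ψ² − d²(3+ψ)/4)]² / (ψd²) = (0.980 + 0.396)² / 0.0162 = 116.9, so 117.
- Connor formula: n = [1.960√ψ + 0.842√(ψ − d²)]² / d² = 118.7, so 119. Power at 117 is 0.794.

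The stated 117 reproduces for the binary primary analysis.

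**2. Change score against baseline adjustment.** For each patient let Y be the difference between treatments in end-of-period values and B the difference in the two period baselines. Baseline is read as the start of each period, since parameters are measured at the beginning and end of each.

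- Change-score contrast: Var(Y − B) = Var Y + Var B − 2Cov(Y,B).
- Adjusted contrast, large sample: Var Y − Cov(Y,B)²/Var B.
- The first minus the second equals (Var B − Cov(Y,B))²/Var B, which is never negative.

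So adjustment cannot have the larger variance, apart from the degree of freedom spent on the slope. With equal variances and r = corr(Y,B), the ratio is 2(1−r)/(1−r²) = 2/(1+r).

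**3. Size.** The article gives no correlations, so these are assumptions. Let w be the correlation of baseline and end value within a period and b the correlation of any two readings from different periods. Then r = (w−b)/(1−b). In units of s², the variances are: change 4(1−w), end value alone 2(1−b), adjusted 2(1−b)(1−r²).

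| b | w | r | Change | End value | Adjusted | Change/adjusted | CI wider by |
|---|---|---|---|---|---|---|---|
| 0.5 | 0.5 | 0 | 2.00 | 1.00 | 1.00 | 2.00 | 41% |
| 0.5 | 0.6 | 0.20 | 1.60 | 1.00 | 0.96 | 1.67 | 29% |
| 0.5 | 0.7 | 0.40 | 1.20 | 1.00 | 0.84 | 1.43 | 20% |
| 0.6 | 0.8 | 0.50 | 0.80 | 0.80 | 0.60 | 1.33 | 15% |
| 0.3 | 0.8 | 0.71 | 0.80 | 1.40 | 0.686 | 1.17 | 8% |

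Over a wider grid (w from 0.3 to 0.8, b from 0.3 to 0.7, b not above w), the variance saved by adjustment is 14% to 50%.

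Change scores are not always worse than raw end values. The two tie when w = (1+b)/2, as in the fourth row, and change scores win when w is larger, as in the last row.

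**4. Continuous iPTH, illustration only.** Assume the response is a cut-point on a normal variable with equal variances and a pure shift. Then 50% against 68% is a shift of z(0.68) − z(0.50) = 0.468 SD. At zero within-patient correlation, n = (1.960 + 0.842)² × 2 / 0.468² = 71.8, so 72 pairs for 80% power, against the stated 117 (119 by Connor). At within-patient correlation 0.5 the figures are 36 against 83 (Connor).

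**The case against.** The strongest reply is that this is a condensed article, that covariates and models are commonly left to a fuller document, and that a paired t-test or Wilcoxon test on within-patient changes is a recognised crossover analysis. The last part stands: nothing here is invalid. The first does not dispose of the point, because the article states a method for the continuous outcomes and lists them. The suggestion replaces a stated choice and does not ask for missing detail.

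A reader might infer more than the text supports in four ways.

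- *That iPTH is never analysed as a continuous variable.* The Statistical methods section speaks of the variables and their changes in general terms that could cover iPTH, and it names ANOVA. What can be said is that no continuous iPTH comparison is specified as an outcome.
- *That subtracting baselines doubles the variance.* That needs readings within a period to correlate no more than readings from different periods. The general result is against baseline adjustment, not against raw end values.
- *That 72 pairs would have sufficed.* That rests on a normal latent response and zero correlation. Doses are titrated against iPTH, calcium and phosphate, so the shape of end-of-period iPTH cannot be presumed.
- *That the primary analysis is wrongly sized.* The 117 reproduces under its stated rates. Any shortfall would need an assumption about loss of patients, which this point does not make.

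The misplaced McNemar is only a slip of wording, since the same section applies the test correctly to the binary primary. The plan also tests for an order effect and analyses the first period separately, so period is not ignored altogether.

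**Conclusion.** The point holds as a matter of efficiency. The stated comparison of continuous outcomes is valid but has larger large-sample variance than a baseline-adjusted one unless the adjustment slope is exactly one. Under equal variances the ratio is 2/(1+r): about 1.3 to 2.0 for the first four correlation pairs tabulated, and down to about 1.17 over the wider range. The direction follows from algebra. The size depends on correlations that the article does not give, and on baseline meaning each period's own start. If one common baseline were meant, it would cancel from the paired difference and this ratio would not apply.

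The missing continuous iPTH outcome is a lost opportunity and does not bias the responder analysis. The gain is probably substantial, but its figure is illustrative. The change is worth making because it is nearly free.

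**What to change.** - Keep the McNemar responder comparison as the primary analysis.
- For calcium, phosphate and the other continuous outcomes, replace the paired tests on change by ANCOVA: regress the within-patient difference in end-of-period values (paricalcitol minus alfacalcidol) on the within-patient difference in period baselines, with sequence coded +½ and −½ as the period term. The intercept is then the treatment effect at equal baselines. Log-transform skewed variables and report ratios.
- Add log iPTH, averaged over the last 4 weeks of each period and analysed the same way, as a pre-specified secondary outcome.
- Remove McNemar from the sentence on ordered or continuous data, and keep Wilcoxon signed ranks as a sensitivity analysis.

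The cost is wording, made before the data are analysed. All the readings are already scheduled and the sample size is unaffected. The model spends one degree of freedom on the baseline slope and one on period, which is negligible at about 117 patients.
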